## Abstract

According to multiple studies, the objective response rate of PD‐1/PD‐L1 inhibitors in the second‐line treatment of unscreened non‐small cell lung cancer (NSCLC) is only approximately 20%. Predictive biomarkers of treatment efficacies are still under investigation. In selected NSCLC patients with PD‐L1 expression ≥ 50%, the response rate of pembrolizumab in first‐line treatment can reach 44.8%. Moreover, patients with a higher tumor mutation burden (TMB) tend to achieve a better response with nivolumab. Besides PD‐L1 expression and TMB, taking all these indicators into consideration would hypothetically maximize the clinical response in a specific subgroup of patients. Our study aims to accumulate large and complete samples and clinical data to verify the biomarkers and their cutoff values related to the efficacy of PD‐1/PD‐L1 inhibitors in Chinese NSCLC patients, and to construct a comprehensive predictive model by combining multi‐omics data with contemporary machine learning techniques. NSCLC patients administered treatment of anti‐PD‐1/PD‐L1 antibodies or a combination with other drugs have been enrolled. The estimated enrollment is 250 participants. A sophisticated predictive model of immunotherapy response in the Chinese population has not yet been developed. It is clinically and practically imperative to comprehensively evaluate the possible indicators of Chinese NSCLC patients through multiple test platforms, such as next generation sequencing, PCR, or immunohistochemistry. This study is registered in the Chinese Clinical Trial Registry (ChiCTR1900021395).

## Introduction

Lung cancer ranks first worldwide in terms of morbidity and mortality among all malignant tumors. In China in 2015, approximately 4.292 million new cases and 2.814 million deaths from cancer were estimated, including approximately 700 000 new lung cancer cases, of which non‐small cell lung cancer (NSCLC) accounts for approximately 85%.^1^ With 14 lung cancer targeting drugs approved by the Food and Drug Administration/National Medical Products Administration, the mode of diagnosis and treatment of lung cancer has developed from the pathology‐based chemo‐monotherapies of the past to the current molecular‐based targeted drugs, which act with higher specificity, a faster response, and lower toxicity.^2^, ^3^, ^4^ EGFR‐tyrosine kinase inhibitors (TKIs, e.g. gefitinib, erlotinib, afatinib, etc.) show both longer median progression‐free survival (mPFS) and objective response rates (ORRs) in first‐line or second‐line treatment of lung cancer. For example, in a phase III study of gefitinib used for the first‐line treatment of NSCLC in East Asia, the one‐year PFS rates were 24.9% with gefitinib and 6.7% with carboplatin‐paclitaxel. In the *EGFR* mutation‐positive subgroup, patients administered gefitinib had longer PFS than others administered chemotherapy (hazard ratio [HR] for progression 0.48, 95% confidence interval [CI] 0.36–0.64; *P* < 0.001; mPFS, 9.5 vs. 6.3 months), but in the *EGFR* mutation‐negative subgroup, patients administered gefitinib had shorter PFS than others administered chemotherapy (HR 2.85, 95% CI 2.05–3.98; *P* < 0.001; mPFS, 5.5 vs. 1.5 months).^5^, ^6^

Recently, research in cancer immunotherapy has been thriving. Inhibition of the immunological checkpoint pathway represented by PD‐1/PD‐L1 in cancer immunotherapy is considered one of the most promising treatment methods. There are currently three PD‐1/PD‐L1 inhibitors approved by the FDA for NSCLC, namely nivolumab,^7^, ^8^ pembrolizumab,^9^ and atezolizumab.^10^ Intriguingly, the clinical application of PD‐1/PD‐L1 inhibitors has been met with controversy. Multiple studies have revealed that the response rate of PD‐1/PD‐L1 inhibitors in second‐line treatment of unscreened NSCLC is merely approximately 20%.^7^, ^8^, ^9^, ^10^, ^11^ Meanwhile, in selected NSCLC patients with PD‐L1 expression ≥ 50%, the response rate of pembrolizumab in first‐line treatment can reach 44.8%.^9^ The CHECKMATE‐026 study focusing on nivolumab in NSCLC first‐line treatment showed no significant improvement in the nivolumab compared to the chemotherapy cohort (PFS 4.2 vs. 5.9 months; OS 14.4 vs. 13.2 months). But retrospective analysis of subgroups according to tumor mutation burden (TMB) found that patients with higher TMB tend to achieve a better response and superior PFS from nivolumab (nivolumab vs. chemotherapy: ORR 47% vs. 28%, mPFS, 9.7 vs. 5.8 months).^12^ In CHECKMATE‐227, among the subgroup patients with high TMBs (≥ 10 mutations/Mbp), patients administered nivolumab plus ipilimumab had longer PFS than those administered chemotherapy.^13^

These results, among others, suggest that not all NSCLC patients benefit from PD‐1/PD‐L1 inhibitors. A better clinical response might be achieved with parallel tests and analyses concerning other biomarkers, including PD‐L1 expression,^14^, ^15^ TMB,^16^, ^17^ metagenomic sequencing of intestinal microbiota, and certain somatic mutations. Taking all of these indicators into consideration would hypothetically maximize the clinical response of a specific subgroup of patients. In the CHECKMATE‐026 trial, patients administered nivolumab with high TMB and PD‐L1 expression ≥ 50% had a higher response rate than patients with high TMB or PD‐L1 expression ≥ 50% administered other treatment (75% vs. 32% vs. 34%).^12^ In KEYNOTE‐028, a study of pembrolizumab treatment across 20 cancer types, higher T‐cell‐inflamed gene‐expression profile (GEP), PD‐L1 expression, and/or TMB were associated with higher response rates and longer PFS. The subgroup of patients with tumors that had both high TMB and high inflammatory markers (GEP or PD‐L1) had the highest likelihood of response.^18^

The expression levels of some proliferation‐associated genes are associated with response to immune checkpoint inhibitors in NSCLC.^19^ Additionally, *JAK1/2* mutations are associated with resistance to anti‐PD‐1/PD‐L1 antibodies^20^ and *MDM2/MDM4* and *EGFR* alterations may correlate with hyperprogression.^21^, ^22^ The National Comprehensive Cancer Network guideline for NSCLC recommends PD‐1 inhibitors as first‐line treatment for patients with PD‐L1 expression ≥ 50% without *EGFR* or *ALK* mutations, and pembrolizumab for patients with PD‐L1 expression ≥ 1% as second‐line treatment. In January 2018, multiple studies confirmed that the composition of specific intestinal microbiota in Western populations significantly prolonged PFS in patients treated with PD‐1/PD‐L1 inhibitors.^23^, ^24^ However, a sophisticated predictive model of immunotherapy response in the Chinese population has not yet been developed. It is clinically and practically imperative to comprehensively evaluate the possible indicators of Chinese NSCLC patients through multiple test platforms, such as next generation sequencing (NGS), PCR, or immunohistochemistry (IHC).

## Methods

### Objectives

The main purposes of this prospective observational study are to accumulate large and complete samples and clinical data to verify the biomarkers and their cutoff values related to the efficacy of PD‐1/PD‐L1 inhibitors in Chinese NSCLC patients, and to construct a comprehensive predictive model from the data. The secondary purposes are to explore the relationship between numbers and/or frequencies of certain genetic variations (single nucleotide variations, insertions and deletions, copy number variations) and immunotherapy response, and to verify the influence of known DNA repair‐related genes on immunotherapy resistance and/or hyperprogressive disease. This study will also focus on the application of liquid biopsy, especially the mutation spectrum and TMB in circulating tumor DNA (ctDNA) for discriminating pseudoprogression and predicting resistance or progression of immunotherapy. An evaluation of intestinal microbiota metagenomic sequencing, based on the efficacy of PD‐1/PD‐L1 inhibitors and changes in intestinal microecology in Chinese tumor patients, will also be conducted in conditional research centers.

### Eligibility criteria

The estimated enrollment is 250 participants. Enrollment is limited to patients: aged 18–75 years old; with histologically or cytologically confirmed metastatic or local advanced NSCLC; without any *EGFR* or *ALK* genetic alteration (common or uncommon); administered anti‐PD‐1/PD‐L1 antibodies or a combination with other drugs; with available tumor tissue samples within two years before treatment or undergoing biopsies; with no less than 15 formalin‐fixed paraffin‐embedded samples; with available peripheral blood samples obtained within one week before treatment, and six weeks, three months and six months after treatment, and at the time point of withdrawal (10 mL each sample); at least one measurable lesion according to Response Evaluation Criteria in Solid Tumors (RECIST) version 1.1; Eastern Cooperative Oncology Group performance status (ECOG PS) score of 0 or 1; life expectancy of at least 12 weeks; and with adequate organ function and hematopoiesis. Subjects with a history of hematologic or primary solid tumor malignancy within five years prior to the first study treatment are excluded. The ethics committees at Zhongshan Hospital of Fudan University and each institution approved this study and written informed consent will be obtained from each patient.

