**Figure 1 tca13078-fig-0001:**
[figure not shown]
Study schema of ChiCTR1900021395. CNV, copy number variation, FFPE, formalin‐fixed, paraffin‐embedded; GEP, gene‐expression profile; IHC, immunohistochemistry; Indel, insertions and deletions; NSCLC, non‐small cell lung cancer; SNV, single nucleotide variations.

The primary efficacy endpoint is to identify a novel predictive model for ORR and PFS after treatment via a comprehensive association analysis using multi‐omics data. For baseline evaluation, formalin‐fixed paraffin‐embedded tumor tissues, 10 mL of peripheral blood, and 5 mL of fasting stool in the morning will be collected from registered patients before treatment. Six weeks, three months and six months after the initiation of PD‐1/PD‐L1 treatment, 10 mL of peripheral blood will be sampled from patients that are still involved. If the treatment needs to be discontinued as the result of disease progression or intolerable toxicity, 10 mL of peripheral blood and 5 mL of fasting stool in the morning will be collected at the point of patient withdrawal. Consents will be completed and archived at each surveillance and sample collection. All data should be available for analysis by the end of 2019 (Table 1).

**Table 1 tca13078-tbl-0001:** Project flow chart

Stage	Baseline	Supervision period			
	V0	V1	V2	V3	Vx
Item	‐1–0 weeks	6 weeks ± 3 days	3 months ± 3 days	6 months ± 3 days	Discontinued
General information	×				
Pathology Report	×				
Eligibility criteria	×				
Informed consent	×				
FFPE samples	×				
Blood samples	×	×	×	×	×
Stool samples	×				×
CRF	×	×	×	×	×
Adverse reactions	×	×	×	×	×

CRF, case report form; FFPE, formalin‐fixed paraffin‐embedded.

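### Follow-up blood samples are written into the enrolment criteria, which contradicts the sampling rule and Table 1 and, if applied literally, would select patients on outcome

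*Protocol article*

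**What the plan says.** Eligibility criteria opens its list with "Enrollment is limited to patients". One item in that list reads "with available peripheral blood samples obtained within one week before treatment, and six weeks, three months and six months after treatment", and it goes on to require a further sample at withdrawal. The items are joined by a plain conjunction. Nothing limits the later samples to patients still on study, and nothing turns the condition into a willingness to give them. The same list asks for "life expectancy of at least 12 weeks".

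Study design and treatment plan (the text after Figure 1) gives a different rule for the same time points: "10 mL of peripheral blood will be sampled from patients that are still involved". For early stoppers it begins "If the treatment needs to be discontinued as the result of disease progression or intolerable toxicity" and provides for blood and stool at withdrawal. Table 1 ticks eligibility and informed consent at V0 only (-1 to 0 weeks) and has a separate column, Vx, for discontinuation.

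The primary endpoint in that section is to "identify a novel predictive model for ORR and PFS after treatment".

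**The concern.** An enrolment condition should be decidable when the patient enters. Whether someone has a six-month sample is known only six months later, after much of the response and PFS information has accrued. A cohort defined by that sample is conditioned on remaining under observation for six months, the usual route to immortal-time selection.

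Two things would be at stake:

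- **The primary model.** Biomarker associations, cutoffs and model performance would come from patients who stayed long enough to be sampled. The model is meant for a patient about to start treatment, and such a cohort does not represent that patient.
- **The secondary aims.** Objectives includes resistance and hyperprogressive disease, and Analytical methods includes separating pseudoprogression from true progression. Patients who leave early carry much of that information.

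A literal reading is not far-fetched in practice. Objectives names large and complete samples as a main purpose, several centres take part, and the Abstract says enrolment has already begun. Nothing in the article says which of the two rules governs.

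**Working it through.** **Setting the passages side by side**

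1. Eligibility criteria requires samples at baseline, six weeks, three months, six months and withdrawal. Table 1 assesses eligibility only at V0, when just the baseline sample can exist. The criterion cannot be assessed there as written.
2. Study design and treatment plan treats a patient who stops early for progression or toxicity as a study patient with a withdrawal visit. Under the literal criterion, the same patient fails enrolment if the stop comes before six months.
3. The list asks for a life expectancy of 12 weeks, under three months. It therefore admits patients who are not expected to reach the six-month sample that it also requires.

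**Hypothetical size under the literal criterion**

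The article gives no calculation to reproduce. The enrolment of 250 has no stated derivation, and this point does not dispute it. The article also states no expected PFS or dropout for this cohort, so the inputs are borrowed or assumed:

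- Median PFS *m* = 4.2 months (first-line nivolumab) and 9.7 months (its high-TMB subgroup). Both are results of a trial cited in the Introduction.
- Exponential PFS (assumption).
- Sampling ends at progression (assumption).

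The share still sampled at *t* months is S(t) = 2^(−t/m). Six weeks is 6 / (365.25/12/7) = 1.38 months.

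| Median PFS | S(6 weeks) | S(3 months) | S(6 months) | Without a six-month sample | Of 250 |
|---|---|---|---|---|---|
| 4.2 months | 0.796 | 0.610 | 2^(−6/4.2) = 0.371 | 1 − 0.371 = 63% | 157 |
| 9.7 months | 0.906 | 0.807 | 2^(−6/9.7) = 0.651 | 1 − 0.651 = 35% | 87 |

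So about 93 or 163 of 250 would reach the six-month sample. If the rule in Study design and treatment plan governs, no patient is lost through eligibility and all 250 stay in.

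**The case against.** The best defence is that this is a sampling schedule misplaced in the eligibility list of a condensed article. Much supports it. The study is described as prospective. Baseline material is collected from registered patients before treatment, so registration comes before every follow-up sample. Table 1 settles eligibility at V0. The 12-week life expectancy would serve little purpose beside a real six-month condition. The withdrawal sample is impossible as an entry condition, because nobody could then enrol before leaving the study. On this reading eligibility causes no selection, and the defence stands as the likelier intention.

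A reader might therefore go too far in three ways:

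- **That early progressors and early deaths cannot qualify.** This follows only from Eligibility criteria read alone. The design section and Table 1 let them in.
- **That no PFS event could occur in the first six months.** The criterion asks for a sample, not freedom from progression. The article does not say that every progression ends participation, and it plans to study pseudoprogression.
- **That the response rate would be inflated by a known amount.** Any such figure would pair a response rate of about 20% in unselected second-line patients with PFS medians from a first-line trial. This cohort has no stated line of treatment and allows combinations.

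It is also fair to say that analysis sets are commonly left to the SAP or full protocol, and nothing here restricts the response and PFS analysis to patients with complete serial blood. That limits the finding to the stated criterion. It does not remove the contradiction.

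**Conclusion.** The criterion is wrongly stated. It makes enrolment depend on samples that cannot exist when eligibility is checked, and it contradicts the article's own sampling rule and visit table. The article does not show that survivors alone are being enrolled. The harm is conditional: it arises if a site applies the criterion literally, or if the criterion is later used to define who is evaluable.

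In that case the cohort would be selected on the outcomes being modelled and would lose many early progressors. The 35–63% range for patients without a six-month sample rests on exponential PFS, sampling that stops at progression, and medians borrowed from another trial. Sampling beyond progression would make it smaller. The contradiction itself needs none of these assumptions.

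**What to change.** Reconcile Eligibility criteria with Study design and treatment plan and Table 1:

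- Make only baseline tissue and baseline blood conditions of enrolment, together with consent to serial sampling.
- Leave the six-week, three-month, six-month and withdrawal samples to the visit schedule, collected while the patient remains on study or at discontinuation.
- State that every enrolled, treated patient stays in the response and PFS model, whatever later samples exist. Analyses of serial ctDNA will use those who gave the samples, and that needs no entry rule.

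Because enrolment has begun, the sponsor should also confirm that no centre has left out or removed a patient for lack of a later sample.

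The wording change is about one sentence in the eligibility list and adds no visits. The cost is that some patients will have incomplete serial blood, which the design section already expects.

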### Study design and treatment plan

This study is a prospective, single‐arm, observational study. Primary tumor tissues, serial liquid biopsies, and stool samples will be obtained from patients with advanced NSCLC, with no *EGFR* or *ALK* genomic tumor aberrations treated with PD‐1 or PD‐L1 inhibitors (Fig 1).

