## Discussion

The primary goal of this study is to establish a multicenter cohort of NSCLC patients in China. This result will complement current understanding of the use of PD‐1/PD‐L1 inhibitors to predict biomarkers in advanced Chinese NSCLC patients and explore the relevant influencing factors. Through long‐term follow‐up of patients, we can further improve real‐world multicenter data of the efficacy of advanced NSCLC immunotherapy in China.^25^

This multicenter prospective study will deepen the mining of multiple biomarkers, establish a comprehensive forecasting model, and predict the sensitivity of treatment in multiple dimensions. We believe that biomarkers indicating the efficacy of PD‐1 can be integrated into a mathematical model, which will greatly improve the predictive value of immunotherapy.

However, this study does have potential limitations, such as the inconsistencies and incompleteness of clinical practice data sources; diagnostic bias among different institutions; the fact that blinding is not performed in a real‐world study; and intervention by external clinical trial participants. Research methods with higher statistical power will help to reduce these biases.

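### In a single-arm cohort where every patient receives a PD-1/PD-L1 inhibitor, the PFS model can forecast outcome under treatment but cannot show that a marker or cutoff relates to drug efficacy or predicts sensitivity to treatment

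*Protocol article*

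**What the plan says.** The design section of the protocol article is explicit: "This study is a prospective, single‐arm, observational study". Eligibility criteria limit enrolment to patients "administered anti‐PD‐1/PD‐L1 antibodies or a combination with other drugs", so there are no unexposed patients. The article describes no concurrent, historical or external comparator.

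The text after Figure 1 gives the primary endpoint: to "identify a novel predictive model for ORR and PFS after treatment via a comprehensive association analysis using multi‐omics data". Two other places describe the product in stronger terms. The Objectives want to "verify the biomarkers and their cutoff values related to the efficacy of PD‐1/PD‐L1 inhibitors in Chinese NSCLC patients". The Discussion says the study will "establish a comprehensive forecasting model, and predict the sensitivity of treatment in multiple dimensions".

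The limitations paragraph of the Discussion covers inconsistent and incomplete data sources, diagnostic differences between institutions, lack of blinding and outside trial participation. It does not mention the missing comparator. It closes by saying that methods with more statistical power will help to reduce the biases listed.

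**The concern.** Efficacy and sensitivity to treatment are statements about what the drug changes. For a time-to-event outcome such as PFS, they require knowing how marker-positive and marker-negative patients would have fared without the drug. A marker of slow natural course lengthens PFS under any therapy. In a cohort where everyone is treated, it appears as a strong association and enters the model beside markers that truly modify the drug effect.

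What is at stake is the meaning of the primary result. If the PFS model and its cutoffs are reported as markers of efficacy, a reader cannot tell which part is prognosis and which part is drug effect, and the report would not warn that the two are mixed. The forecast itself is not in doubt.

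**Working it through.** There is no plan figure to reproduce. The enrolment of 250 comes without an effect size or error rates in this article, which is not held against it. The question is whether the quantity can be identified at all.

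**Step 1. What one arm can estimate.** For a binary marker,

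log HR(marker, treated) = log HR(marker, control) + log HR(marker-by-treatment).

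The left side is estimable here. The first term on the right is prognosis and the second is treatment-specific. With no control arm there is one equation and two unknowns.

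**Step 2. The article's own comparative example.** The Introduction gives median PFS by EGFR status for gefitinib and chemotherapy. Marker-positive: 9.5 months on gefitinib, 6.3 on chemotherapy. Marker-negative: 5.5 and 1.5 months, read here as 1.5 on gefitinib and 5.5 on chemotherapy, because the text says gefitinib was shorter (HR 2.85).

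- Positive/negative ratio on gefitinib: 9.5/1.5 = 6.33
- Positive/negative ratio on chemotherapy: 6.3/5.5 = 1.15
- Ratio of ratios: 6.33/1.15 = 5.53 (unrounded inputs)
- On the hazard ratio scale: 0.48/2.85 = 0.168

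A gefitinib-only cohort would have seen 6.33 and could not have divided it into 1.15 and 5.53. Most of the 6.33 was treatment-specific in this case, but only the chemotherapy arm shows it. The high-TMB evidence has the same comparative form: "nivolumab vs. chemotherapy: ORR 47% vs. 28%, mPFS, 9.7 vs. 5.8 months".

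**Step 3. Same treated arm, three different truths.** Assumptions: exponential PFS, so that HR(+/−) = median(−)/median(+), and treated medians of 9.7 months (marker-positive) and 4.2 months (marker-negative). Both numbers appear in the Introduction, but the pairing is only illustrative: 4.2 is the overall nivolumab median, not a marker-negative figure. All control medians are assumed.

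| Truth | Control medians, +/− (months) | HR in treated | HR in control | Marker-by-treatment HR |
|---|---|---|---|---|
| Purely prognostic | 9.7 / 4.2 | 4.2/9.7 = 0.433 | 4.2/9.7 = 0.433 | 0.433/0.433 = 1.00 |
| Mixed | 5.8 / 4.2 | 0.433 | 4.2/5.8 = 0.724 | 0.433/0.724 = 0.598 |
| Purely treatment-specific | 4.2 / 4.2 | 0.433 | 1.00 | 0.433/1.00 = 0.433 |

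The data this study would collect have the same distribution in all three rows.

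**Step 4. Does sample size help?** Take the purely prognostic row, 50% marker prevalence (assumed) and 150 PFS events (assumed). Then z = |ln 0.433| × √(150 × 0.25) = 0.837 × 6.124 = 5.13, and power = Φ(5.13 − 1.96) = 0.999. In 4,000 simulated cohorts of 250 patients with all events observed, the marker was significant in every one. More events narrow the interval around 0.433 and leave the last column of the table undetermined.

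**Step 5. Objective response.** Response under monotherapy is less exposed, on the general assumption that tumours seldom shrink untreated. Eligibility allows combinations, however, and the article's own 28% response rate on chemotherapy shows that another drug can produce responses. The partner drugs and the monotherapy/combination split are not given.

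**The case against.** The strongest reply is that the word predictive can simply mean forecasting. The primary endpoint concerns ORR and PFS after treatment, obtained by association analysis, and the Discussion also calls the product a forecasting model. One arm can deliver that. This stands, and it means the primary endpoint is achievable as a forecast. It does not cover the Objectives and the Discussion, where efficacy and treatment sensitivity are claimed. No analysis plan could add a comparator to this cohort.

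Single-arm cohorts are also normal for exploratory biomarker work. That stands too: the design is not an error, and no control arm is asked for.

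Four stronger readings are tempting, and the documents do not support them.

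- A reader might infer that the model will direct patients to or away from these drugs. Methods states no treatment-assignment rule, so that use is not documented.
- A reader might take 5.9 months on chemotherapy overall and 5.8 in high TMB as proof that TMB is not prognostic. The second group is nested in the first, and no low-TMB figure is given.
- A reader might treat the 0.999 above as a false-positive rate. It is ordinary power to detect a real association, under assumed inputs. It shows only that significance does not distinguish the three truths.
- A reader might expect adjustment for clinical factors to cure the problem. It removes only prognosis those factors capture; an independent omics marker of slow natural course would remain.

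**Conclusion.** The point holds in a limited form. The PFS model and its cutoffs can estimate outcome under PD-1/PD-L1 treatment. They cannot establish that a marker relates to the drugs' efficacy or predicts sensitivity to them, and the article claims both without naming the missing comparator as a limitation. Its remark about statistical power would not apply to this limitation.

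The size is a matter of identifiability, not of an error rate: in the illustration, one observable hazard ratio of 0.433 is compatible with a marker-by-treatment hazard ratio anywhere from 1.00 to 0.433 among the three truths considered. Those values rest on exponential PFS and assumed medians; the conclusion does not. It needs only one arm with everyone treated. For objective response the problem is smaller under monotherapy and returns in part under combinations. The change is worth making because it alters what the study may conclude, but it does not invalidate the study.

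**What to change.** 1. **Reword.** In the objective, primary endpoint and conclusions, state that the PFS model and cutoffs estimate outcome under PD-1/PD-L1 treatment and do not by themselves support treatment selection.
2. **Add a limitation.** Name the absence of a comparator, say that prognostic and treatment-specific associations cannot be separated for PFS, and say that higher statistical power does not remove this.
3. **Place the sensitivity claim.** Rest any such claim mainly on objective response, reported separately for monotherapy and combination patients.
4. **Supporting analysis.** Report what the omics layers add to a model of whatever baseline clinical factors are collected. ECOG PS and disease extent are at least assessed for eligibility; the article does not list the case report form fields. State that this reduces measured prognostic confounding and does not identify a treatment interaction.

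Items 1 and 2 are the essential part. No new patients or samples are needed. The cost is one additional model, a more modest claim, and smaller groups for the response analysis, of a size the article does not allow one to calculate.
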